### Randomisation

A randomised block design will be adopted with admission time being the matching factor. Specifically, four adjacent patients who are admitted in the same month will be considered as a block. Within each block, the four subjects can be arranged in six distinct permutations: AABB, ABAB, ABBA, BAAB, BABA and BBAA, corresponding to the random numbers 1–6, respectively. These permutations are then randomly assigned to two groups, designated as group A and B. Following the determination of the arrangements, the subsequent phase entails a random selection from the six pre-established sequences. For each selection, a number is randomly drawn from the set ranging from 1 to 6. For example, the selection of the number 5 is specifically designated to represent the ‘BABA’ arrangement. The four subjects who enter this block are assigned to groups B, A, B and A, respectively. Random numbers ranging from 1 to 6 will be generated by a research assistant, who is blinded to the trial, using a personal computer prior to the commencement of patient recruitment. Subsequently, the random numbers will be concealed in sequentially coded, opaque and sealed envelopes and opened by another research assistant.

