**Trial registration number:**

ChiCTR2300069333.

STRENGTHS AND LIMITATIONS OF THIS STUDYThis is a prospective, randomised controlled, non-inferiority clinical study to compare the surgical procedure of unilateral biportal endoscopic transforaminal lumbar interbody fusion (TLIF) with microscopic tubular technique TLIF for the treatment of degenerative lumbar spinal stenosis in terms of the clinical safety and efficacy.All surgeries are performed by surgeons who have 10-year operation experience and are familiar with the two surgical procedures.The data are collected from a single institution with a relatively small sample size.The surgeons cannot be blinded for the study because the intervention is surgery and the protocols for two surgeries are different.

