## Discussion

The current protocol describes the rationale, non-inferiority design and methods of this randomised, controlled clinical trial that compares the efficacy and safety of UBE-TLIF to MT-TLIF in patients of DLSS. The non-inferiority design can not only demonstrate the efficacy of UBE-TLIF compared with MT-TLIF but also focus on exploring the advantages beyond efficacy. Furthermore, it can avoid ethical concerns and has more ethical value than placebo-controlled or no-treatment-controlled clinical trials.^33^ Moreover, to avoid potential bias, all surgeries are performed by surgeons who have 10-year operation experience and are familiar with the two surgical procedures.

Moreover, the primary outcome in this study is the ODI score at 1-year postoperation. MCID was used to determine the sample size of this trial, which may facilitate the final analysis. Additionally, a majority of the outcomes in this study are self-reported by the subjects, including the VAS score, ODI score, SF-36 questionnaire and EQ-5D questionnaire, which will help minimise observation bias to some extent.

However, there are still some potential limitations that need to be addressed. The surgeon cannot be blinded for the study because the protocols for the two surgeries are different. However, to reduce bias as much as possible, investigators who are blinded in the group assignment process will perform the clinical assessment, including baseline evaluation. Additionally, all data will be collected from a single institution with a relatively small patient number. Larger multicentre studies are needed to confirm the efficacy and safety of MT-TLIF and UBE-TLIF in treating DLSS in future.

In conclusion, this study aims to compare the efficacy and safety of MT-TLIF and UBE-TLIF in treating patients with DLSS. The completion of this study will not only examine the use of UBE-TLIF in lumbar spinal stenosis but also provide helpful clinical references.

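### As described, each sealed envelope holds a number that codes four allocations, so opening it for a block's first patient can show the opener up to three later ones

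*Protocol article*

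**What the plan says.** All the elements are in the Randomisation section of the protocol article.

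- **Block:** "four adjacent patients who are admitted in the same month will be considered as a block".
- **Coding:** the six sequences are "AABB, ABAB, ABBA, BAAB, BABA and BBAA, corresponding to the random numbers 1–6, respectively".
- **One number covers a whole block:** in the article's example, "the selection of the number 5 is specifically designated to represent the ‘BABA’ arrangement", and then "The four subjects who enter this block are assigned to groups B, A, B and A, respectively".
- **What is generated:** "Random numbers ranging from 1 to 6 will be generated by a research assistant, who is blinded to the trial", before recruitment starts.
- **What is sealed, and who opens it:** "the random numbers will be concealed in sequentially coded, opaque and sealed envelopes and opened by another research assistant".

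Three other places bear on the consequences. The Strengths and limitations box states: "The surgeons cannot be blinded for the study because the intervention is surgery", and the Discussion repeats this: "The surgeon cannot be blinded for the study because the protocols for the two surgeries are different". The last exclusion criterion in Table 1 lets the surgeons exclude a patient for other diseases that they consider unsuitable. Under Patient selection, a trained research nurse presents the trial to patients.

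**The concern.** A sealed envelope protects allocation only if it holds nothing about patients who have not yet been enrolled. Here the sealed item is the block number, and that number settles four assignments at once. Someone who opens it for the first patient can read off the next three.

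If that knowledge reached anyone who screens, schedules or judges eligibility, the next patient could be included, deferred or excluded in the light of the arm waiting for them. Block position follows admission order, and the surgeon-judged exclusion offers one route. The resulting imbalance would enter the 1-year ODI comparison, for which Statistical analysis names an independent t-test and no covariate adjustment. Adjustment could in any case deal only with measured factors.

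A separate, smaller weakness is that the block size is always four. Even with one allocation per envelope, an observer who follows past assignments can work out some of those to come.

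**Working it through.** **Inputs.** Block size 4, six sequences and one number per block (Randomisation). N = 96 at 1:1 (Study design and settings). SD 13, margin 8, true difference 0, one-sided α = 0.025, power 0.8 and 10% loss (Sample size).

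**The plan's own figures reproduce.** The number of balanced sequences of four is C(4,2) = 6, as stated. For the sample size, the exact t calculation needs 43 per arm (power 0.805), and 86/0.9 = 95.6, rounded up to 96. The normal approximation gives 42 per arm and 94 in total. The point below does not affect the sample size.

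**A. Block number in the envelope, patients allocated one at a time.**
- A block that receives k patients shows the opener k − 1 later allocations.
- Over the trial, the number shown in advance is 96 minus the number of blocks used.
- If every block fills, there are 96/4 = 24 blocks and 96 − 24 = 72 allocations (75%).
- The same-month rule may leave blocks incomplete. More blocks are then used and the count falls, so 72 is a maximum.
- The opener's best-guess accuracy in full blocks is (0.5 + 3)/4 = 87.5%.

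**B. One allocation per envelope, fixed block of four.** The observer is assumed to know the block size, the block boundaries and all past allocations.

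| Position in block | Known with certainty | Best guess correct |
|---|---|---|
| 1 | 0 | 1/2 |
| 2 | 0 | 2/3 |
| 3 | 2/6 (AABB, BBAA) | 1/3 × 1 + 2/3 × 1/2 = 2/3 |
| 4 | 1 | 1 |
| Sum | 1.333 | 2.833 |

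- Certain: 1.333/4 = 33.3%, or 32 of 96.
- Best guess: 2.833/4 = 70.8%, against 50% with no information.
- For comparison, a known fixed block of six gives 25.0% certain and 68.3% accuracy. Enlarging a block that remains known gains little; the benefit comes from varying the size and not disclosing it. The predictability of an undisclosed mix of 4 and 6 was not computed.

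**C. What a bias would do (illustration only).** The documents give no basis for the size of any selection bias, so 2 to 3 ODI points in favour of UBE-TLIF is an assumption.
- SE = 13 × √(2/43) = 2.80.
- With a true difference at the margin of 8, the normal-approximation chance of wrongly declaring non-inferiority is Φ(−1.96 + bias/2.80).
- Bias 0 gives 2.5%; bias 2 gives Φ(−1.25), about 11%; bias 3 gives Φ(−0.89), about 19%.

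**The case against.** The strongest reply is that the article condenses its procedure and the text is being read too literally. It does not give the number of envelopes, when they are opened or what the opener passes on, so one envelope per patient is not ruled out. It does provide a list made before recruitment, ordered opaque envelopes and a second assistant to open them. A research nurse, not that assistant, is described as presenting the trial. A block might also be opened only once all four patients have entered, and then no future allocation is shown.

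Much of this stands as a limit on the consequences. A reader might infer that concealment has failed for most patients, or that recruiting staff know 72 of 96 allocations. The documents support neither: they do not say that the envelope content reaches anyone who recruits or judges eligibility. A reader might also describe the centre as unblinded, which is wrong. Under Blinding, patients, clinical assessors and the raw data for analysis are kept blind to group; only the surgeons are said to be unblinded. The discretionary exclusion covers other diseases and is not a general power to choose cases. Fixed blocks are a common choice, and the figures in B require a fully informed observer.

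What does not stand is the claim that this is mere brevity. The article states what is generated, what it codes, what is sealed and who opens it, and that mechanism, followed as written, shows later allocations. Opening only after four entries is not stated, and it would not remove the smaller predictability of a fixed block of four.

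**Conclusion.** The point holds as a flaw in the stated mechanism. The envelopes are described as holding block-level numbers, so the opener can learn up to three later allocations per block, and at most 72 of 96. That maximum assumes that all 24 blocks fill and that patients are allocated one at a time. Leakage to recruiters or surgeons is a risk and not a documented fact. Even so, nothing separates the opener from screening or scheduling, the surgeons are unblinded, and they hold a discretionary exclusion for other diseases. Concealment is therefore not protected by the procedure as written.

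The fixed block size is secondary. With patient-level envelopes it leaves 33.3% of allocations certain and a best-guess accuracy of 70.8%, for an observer who knows the block size, the boundaries and every past allocation. That any recruiter has this knowledge is an assumption, although the article describes no masking or variation of the block size. The direction and size of any effect on ODI cannot be derived from the documents.

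**What to change.** 1. Before recruitment, or for the unused part of the list, expand the block numbers into individual allocations and place one patient's allocation in each sequentially numbered opaque envelope.
2. State that each envelope is opened only after consent, eligibility confirmation and baseline assessment, by an existing staff member with no recruitment role.
3. As a secondary and cheap improvement, generate the list with randomly varying block sizes (for example 4 and 6) that are not disclosed to recruiting or surgical staff.
4. If patient-level envelopes were in fact used, correct the sentence in the Randomisation section. If block-level envelopes were used, report this and examine baseline balance by position within the block.

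**Cost.** One envelope per patient means 96 envelopes; one per block would be 96/4 = 24 if every block fills (the article gives neither count). The unused list must be regenerated. Varying the block size gives slightly less exact balance by month. No extra staff or patients are needed, and the sample size does not change.

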### Blinding

Since the wounds on the body surface are basically the same size after surgery, the subjects do not know their specific surgical methods. The clinical assessment process, including baseline levels and self-report questionnaires, will be performed by clinicians who are unaware of subject group assignments. Evaluation data will be stored in electronic medical records and collected in parts according to the case report form (CRF). Statistics can only be carried out after all data are collected. All statistical raw data do not provide grouping information. The main researcher will provide specific information on grouping after all information has been entered.

### Baseline data

Baseline data including demographics, comorbidity, ODI score, Visual Analogue Scale (VAS) score, 36-Item Short Form Survey (SF-36) and EuroQol 5 Dimensions (EQ-5D) questionnaire will be collected. X-rays that measure the DH of operated level and lumbar lordosis (LL) angles will be conducted. DH can be calculated as the average value of the height from anterior part, middle part and posterior part in the same disc. LL angle is defined as the angle between the upper endplate of vertebra Lumbar one and Sacral 1.^15^,^17^

### Surgical procedure

To avoid technical bias, all surgeries are performed by surgeons who have at least 10 years surgical experience and are familiar with the two surgical procedures (more than 100 cases of experience).

For UBE-TLIF,^18^ observation and operation channels are established independently without intrainterfering. The endoscope used in this operation will be the same one that used for the knee arthroscope. After attaching the spinal endoscope, the rongeur removes part of the lamina, followed by ligamentum flavum resection and further nerve decompression. Then the annulus fibrosus will be separated, and the degenerated intervertebral disc tissue will be removed to process the cartilage endplate. The removed autologous bone will be attached to a allograft bone before inserting it into a suitable cage which further to be implanted into the intervertebral space through the operation channel. Finally, percutaneous pedicle screws will be inserted and fixed.

For MT-TLIF,^18^ a working channel is established within the intermuscular space of the multifidus muscle. Specifically, a 3.5–4.5 cm longitudinal incision will be made. Then, a series of dilators ranging from small to large are inserted and a suitable tubular retractor is placed. With the aid of microscope, part of the articular processes, laminae and corresponding ligamentum flavum will be removed to decompress the nerve root and dural sac. Then the intervertebral disc will be removed to process the cartilage endplate. A single fusion cage with autologous and allogeneic bone will be inserted before placing percutaneous pedicle screws and fixation rods.

### Outcome measurements

#### Primary outcome

The main outcome of the study is the ODI score at 1-year postoperation, which is a 10-item questionnaire specific to low back pain patients, including pain intensity, personal care (washing, dressing etc), lifting, walking, sitting, standing, sleeping, sex life (if applicable), social life and travelling. Each of the 10 items is scored from 0 to 5. Total scores are calculated by dividing the actual by the maximum score of 50 and converting it to a percentage. The score of 100% is recognised as the highest score, signifying the greatest dysfunction severity.^19 20^

The minimal clinically important difference (MCID) is a threshold value that patients and clinicians perceive as clinically meaningful. The clinically acceptable MCID in reported ODI scores is 8–12. However, to date, there is no consensus on calculating the optimal MCID for the ODI scores in groups.^21^,^23^ Consequently, following discussion, we adopted 8 as the MCID within clinically acceptable range. By comparing the ODI score 1 year after surgery, we can determine whether UBE-TLIF is not inferior to MT-TLIF within the non-inferiority margin of 8.

Considering that the condition of most enrolled subjects will be stabilised at 1-year postoperation, the assessment time frame of 1-year ODI is between 12 and 15 months after the operation. In case subjects do not return to the hospital for follow-up on time during this period, a telephone follow-up will be conducted to complete the ODI questionnaire.

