#### ODI score

The ODI scores were assessed at 1 month, 3 months and 6 months postoperatively. Scores are determined following the aforementioned method.

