### Sample size

The MCID for ODI scores reported in similar studies is 8–12.^22 23^ After discussing among experienced professors from the spine surgery department, 8 in ODI score is chosen as the margin of non-inferiority (ðN) in this study. Based on the Consolidated Standards of Reporting Trials 2010 statement,^28^ it is assumed that the expected response is the same in both groups, the estimated true difference between the two surgeries is 0, and the ðN is 8. The SD is estimated to be 13 based on previous studies.^29^ The test level is one sided (α=0.025), and the test power (1−β) is 0.8. Considering that 10% of population may loss to follow-up, a total of 96 subjects are required in this clinical study.

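### The ODI is always scored out of 50 although its sex-life item may not apply, so a patient who leaves that item out scores a tenth too low on the primary endpoint

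*Protocol article*

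**What the plan says.** The Primary outcome section of the protocol article lists the ten ODI items, the last three being "sex life (if applicable), social life and travelling". It continues "Each of the 10 items is scored from 0 to 5" and then gives the scoring rule: "Total scores are calculated by dividing the actual by the maximum score of 50 and converting it to a percentage". The top of the scale is defined as well: "The score of 100% is recognised as the highest score, signifying the greatest dysfunction severity".

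The ODI score section carries the rule to 1, 3 and 6 months: "Scores are determined following the aforementioned method". No section reduces the denominator when the sex-life item does not apply. The Statistical analysis section names last and baseline observation carried forward for missing data, but gives no rule for single items.

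The 1-year score is judged against a fixed margin: "we can determine whether UBE-TLIF is not inferior to MT-TLIF within the non-inferiority margin of 8".

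**The concern.** The optional item and the fixed denominator do not fit together. A total of 50 can be reached only when all ten items are answered. Dividing a nine-item sum by 50 has the same effect as recording no disability on the item left out.

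The trial aims to show non-inferiority, so the effect matters for the main claim. If some scores in both arms are scaled down, the difference between arms is scaled down too, while the margin stays at 8. A real deficit at the margin then looks smaller than it is. The situation is foreseeable: the plan itself provides for the item not applying, and it enrols patients up to age 80.

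**Working it through.** **Inputs from the protocol article.** Ten items scored 0 to 5; denominator 50; margin 8; "the estimated true difference between the two surgeries is 0"; "The SD is estimated to be 13 based on previous studies"; one-sided alpha 0.025; power 0.80; 10% loss to follow-up; total 96, allocated 1:1.

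**Assumptions, not in the article.** An inapplicable item adds nothing to the sum. The score prorated over nine items is the correct one, and the margin of 8 and SD of 13 refer to it. Leaving the item out is unrelated to the score. The share s of patients without the item is unknown, so a range is shown. The control (MT-TLIF) mean ODI is taken as 20.

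**1. The plan's sample size.** n per arm = 2 × (1.96 + 0.8416)² × 13² / 8² = 41.5, so 42. The t-based calculation needs 43 (power 0.805). Then 43 / 0.9 = 47.8, so 48 per arm and 96 in total, as stated. I use 43 evaluable patients per arm below.

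**2. One patient.** The nine-item maximum is 9 × 5 = 45, so the stated rule multiplies the prorated score by 45/50 = 0.90. A patient scoring 3 on each of nine items has a sum of 27: 27/50 = 54% under the rule, against 27/45 = 60%. The worst possible nine-item score is 45/50 = 90%.

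**3. Equal shares in both arms.** The observed score is 0.9 times the correct score with probability s, and otherwise equal to it. For an arm with correct mean μ:

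- observed mean = (1 − 0.1s)μ
- observed variance = (1 − 0.19s)(13² + μ²) − [(1 − 0.1s)μ]²

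A true difference of 8 is therefore observed as d = 8(1 − 0.1s), and the margin acts as 8/(1 − 0.1s) on the correct scale. With SE = √[(sum of the two variances)/43], the chance of declaring non-inferiority is Φ((8 − d)/SE − 1.96).

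| Share s in both arms | Observed d | Margin on correct scale | Pooled SD | One-sided error |
|---|---|---|---|---|
| 0% | 8.00 | 8.00 | 13.00 | 0.025 |
| 25% | 7.80 | 8.21 | 12.73 | 0.030 |
| 50% | 7.60 | 8.42 | 12.43 | 0.035 |
| 75% | 7.40 | 8.65 | 12.08 | 0.042 |
| 100% | 7.20 | 8.89 | 11.70 | 0.050 |

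For the last row, SE = 11.70 × √(2/43) = 2.52, and Φ(0.80/2.52 − 1.96) = Φ(−1.64) = 0.050. Control means of 15 and 30 give the same errors to within 0.0001.

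**4. Unequal shares (control mean 20, true difference 8, so UBE-TLIF mean 28).**

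- 30% in MT-TLIF, 50% in UBE-TLIF: 0.95 × 28 − 0.97 × 20 = 26.60 − 19.40 = 7.20; error about 0.048.
- 50% in MT-TLIF, 30% in UBE-TLIF: 0.97 × 28 − 0.95 × 20 = 27.16 − 19.00 = 8.16; error about 0.022.

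With no true difference, the same two patterns shift the estimate by 0.40 points, for and against UBE-TLIF respectively.

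**The case against.** The best defence is that the denominator of 50 follows directly on the statement that there are ten items scored 0 to 5, so it describes a fully answered questionnaire. On this view the article is merely silent on nine items and leaves them to the instrument's own instructions or the full protocol. Part of this stands: the text does not say outright that an inapplicable item counts as zero, and the arithmetic rests on that condition. But the same paragraph that makes the item optional states a single rule without exception, and another section reuses it. Applied as written, it gives a wrong value. That is a rule badly fixed, not detail left out.

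Four stronger readings are tempting, and the document does not support them.

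- **The bias always favours UBE-TLIF.** This follows only when the shares are similar in the two arms. Randomisation and the described patient blinding make that the expected case, but more omission in the MT-TLIF arm can reverse the direction. Nothing in the article suggests that omission differs by arm.
- **Any unanswered item is scored as zero.** Items left blank for other reasons may fall under the missing-data rule or the completeness conditions of the analysis sets. The defect shown here concerns the item that the plan itself makes optional.
- **Change from baseline is distorted.** No such analysis is planned; the primary comparison is of the 1-year scores.
- **Stored item answers make rescoring trivial.** Table 2 lists only the ODI score and does not say that item-level answers are kept.

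**Conclusion.** The scoring rule is wrong as written and of moderate weight. If an inapplicable item adds nothing to the sum, the patient's score is understated by 10% in relative terms and capped at 90%.

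The effect on the trial is real but bounded. With equal shares in both arms it removes at most 0.8 points from a true difference of 8. At shares of 25% to 50% it removes 0.2 to 0.4 points, and the one-sided error becomes about 0.030 to 0.035. The 0.050 at 100% is the upper limit for equal shares, not a forecast. The actual share is unknown. The planned 96 stands, because the margin and SD are taken to be on the correctly scaled score.

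**What to change.** Add to the Primary outcome section: when the sex-life item is not applicable, ODI (%) = sum of answered items / (5 × number of items answered) × 100, so that the denominator is 45. State that this applies at baseline and at every visit, including questionnaires completed by telephone or email, and settle it before unblinding so that the scoring cannot be chosen with the results in view.

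The cost is one sentence and a change to the scoring code, with no change to the sample size. It does require the record to show whether the sex-life item was answered. The sponsor should confirm that the case report form captures this, and not only the total.
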